#### Missing data and sensitivity analyses

2.5.2

As previous studies report notable dropout rates of web-based interventions (Linardon et al., 2018a), and the completer sample represents a subgroup of patients who may have particularly benefited from the intervention (Altman et al., 2001), both completer analyses and intent-to-treat analyses will be conducted. The treatment effects across the samples will be tested using two sensitivity analyses: (1) the conservative *last-observation-carried-forward* (LOCF) method, employing the last available measurement point of each subject, and (2) the *multiple imputations by chained equations* (MICE) approach using each participant's BMI, global eating psychopathology, number of binge-eating episodes determined in the EDE interview, and years since illness onset as predictors.

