#### Randomization and blinding

2.3.1

After completing the diagnostic interview and the baseline assessment, randomization will be performed in a 1:1 ratio by an independent researcher who is not involved in the project using a computer-based algorithm provided by the software *SoSci Survey* (Leiner, 2021). The diagnostic interviews will thus be conducted blindly; that is, the clinical interviewers do not know what treatment a participant will be allocated to in case of inclusion (*allocation sequence concealment*; Altman and Schulz, 2001). During the clinical interviews, participants are told that the assigned waiting time varies randomly between 0 and 12 weeks to prevent frustration, dropout, or other biases in the control group. Following randomization, all participants receive an email with either a code to immediately access the intervention or information that they will receive a code in 12 weeks. Finally, the group allocation variable will be blinded to allow unbiased data analyses. For this purpose, an independent researcher will delete all information in the data set indicating the group membership.

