#### Control group

2.3.3

Patients in the control group will not receive the web-based intervention for BED during the 12-weeks following randomization. To best represent routine care, they are free to seek other forms of professional help, including pharmacological and psychological treatments. All concurrently used healthcare services in the intervention and control group will be captured at each assessment (Roick et al., 2001). Subjects in the control group will receive the intervention after completing the last measurement.

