#### Primary and secondary outcome analyses

2.5.1

To statistically evaluate the effectiveness of the web-based intervention for patients with BED compared to the waitlist control condition, growth models within a multilevel modeling (MLM) framework will be conducted. MLMs are regression-based models that allow considering the nested data structure, i.e., the three repeated assessments (level 1) nested within patients (level 2), define change as a continuous process, and have more power when handling missing data than traditional approaches (Hesser, 2015; Kahn and Schneider, 2013; Tasca and Gallop, 2009). To test whether there is a treatment × time interaction effect, we will set up MLMs of increasing complexity (Kahn and Schneider, 2013). The first model will have only random intercepts on the person-level (level 1), and no predictors will be included. In the second model, the fixed effects of time (study entrance, 6 weeks, 12 weeks) and treatment (intervention versus control group) will be added. In a final model, we will examine if the change in symptom severity differs between the intervention and control group by adding the treatment × time interaction. Model fit of the competing models will be compared employing likelihood ratio tests for nested models and the Akaike Information Criterion. A significant treatment × time-interaction with a more substantial change in participants undergoing the 12 weeks of treatment compared to the waitlist group will indicate confirmation of the hypotheses (Raudenbush and Bryk, 2002). The magnitude of treatment effects will be estimated as Cohen's *d* effect size (Feingold, 2013).

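### LOCF is labelled conservative although its direction of bias is not known in advance, and neither stated sensitivity analysis examines a graded departure from missing at random

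*Protocol article*

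**What the plan says.** Under Primary and secondary outcome analyses (2.5.1), "growth models within a multilevel modeling (MLM) framework will be conducted", with the treatment by time interaction as the test of the hypotheses.

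Under Missing data and sensitivity analyses (2.5.2), the article notes notable dropout in web-based interventions and warns that "the completer sample represents a subgroup of patients who may have particularly benefited from the intervention". It therefore states that "both completer analyses and intent-to-treat analyses will be conducted". It continues: "The treatment effects across the samples will be tested using two sensitivity analyses". The first is "the conservative *last-observation-carried-forward* (LOCF) method, employing the last available measurement point of each subject". The second is MICE with four predictors: BMI, global eating psychopathology, interview-assessed binge episodes and years since onset. No shift or reference-based assumption is described for the imputations.

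Three other statements bear on dropout and change in the waitlist arm:
- Randomization and blinding (2.3.1): participants are told that the waiting time "varies randomly between 0 and 12 weeks to prevent frustration, dropout, or other biases in the control group".
- Control group (2.3.3): during the wait, "they are free to seek other forms of professional help, including pharmacological and psychological treatments".
- Statistical power and sample size (2.6): supplementary power analyses allow for 20% dropout, not split by arm.

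**The concern.** LOCF assumes that nobody changes after their last assessment. It is cautious only when that assumption costs the intervention arm more than the control arm. If waitlist participants tend to improve, through the natural course or through other care, a waitlist dropout held at baseline looks worse than he or she would have been. That widens the difference in favour of the intervention. The same happens if an intervention participant leaves after a good week-6 value and later relapses.

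The label matters because it decides how the result will be read. Agreement between the main analysis and LOCF would be reported as survival of a severe test, when nobody knows beforehand which way that test leans.

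The second analysis does not fill the gap. MICE as described rests on missing at random, as does the multilevel model. Yet section 2.5.2 itself suspects that those who complete are those who benefited, which raises the question whether dropout is related to outcome. LOCF does depart from missing at random, but by one fixed assumption. It cannot show how much worse the dropouts would have to be before the conclusion changes.

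**Working it through.** **1. The plan's own figure.** Inputs from section 2.6: d = 0.50, ICC .40, power .80, alpha .05 (sidedness not stated; two-sided is used here). Use a random-intercept model with times 0, 1, 2 and total SD 1.
- Residual variance: 1 − 0.40 = 0.60
- Variance of a subject's slope: 0.60 / 2 = 0.30
- Slope difference: 0.50 / 2 = 0.25
- n per arm: 2 × (1.96 + 0.84)² × 0.30 / 0.25² ≈ 75.3, rounded up to 76

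The total is 152 with power 0.803, so N = 152 is reproduced. The same model is used below.

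**2. Formula for LOCF.** Let m be an arm's true improvement by week 12 (linear over time), p its dropout share, and s the share of the change that a dropout misses (1 if last seen at baseline, 0.5 if last seen at week 6, 0.75 if half leave at each point). LOCF estimates m × (1 − p × s) in each arm. With equal m in both arms and no true effect, the false difference in favour of the intervention is

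m × s × (waitlist dropout − intervention dropout).

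The values of m, p and s by arm are assumptions, because the article gives none of them.

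**3. No true effect, both arms improve 0.5 SD.**

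| Waitlist / intervention dropout | Timing | LOCF difference |
|---|---|---|
| 30% / 10% | all after baseline | 0.5 × 1 × 0.20 = +0.10 SD |
| 30% / 10% | half after week 6 | 0.5 × 0.75 × 0.20 = +0.075 SD |
| 20% / 20% | either | 0 |
| 10% / 30% | half after week 6 | 0.5 × 0.75 × (−0.20) = −0.075 SD |

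Trials were simulated with 76 per arm, ICC .40 and the two-sided random-intercept treatment by time test on the LOCF data. The test rejected in about 10% of trials in the first row and about 8% in the second, against a nominal 5%. If the waitlist does not change (m = 0), there is no bias at any dropout split.

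**4. A fading gain.** Suppose 20% of each arm leaves after week 6, and a 0.5 SD intervention gain at week 6 is gone by week 12. The carried values leave 0.20 × 0.5 = 0.10 SD of false benefit, even with equal dropout.

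**5. A true effect of 0.50 (waitlist improves 0.25, intervention 0.75).**
- Intervention 30%, waitlist 10%, all after baseline: 0.75 × 0.70 − 0.25 × 0.90 = 0.525 − 0.225 = 0.30
- 20% in each arm, half after week 6: 0.50 × (1 − 0.20 × 0.75) = 0.425
- Waitlist 30%, intervention 10%, half after week 6: 0.75 × 0.925 − 0.25 × 0.775 = 0.694 − 0.194 = 0.50

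LOCF therefore shrinks the effect in the first two cases and leaves it unchanged in the third.

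**6. What a graded analysis would show.** If intervention dropouts end δ SD worse than missing at random predicts, the estimate falls by dropout share × δ. Start from 0.50 and let δ run from 0.25 to 1.0:
- 20% dropout: 0.50 − 0.05 = 0.45, down to 0.50 − 0.20 = 0.30
- 30% dropout: 0.50 − 0.075 = 0.425, down to 0.50 − 0.30 = 0.20

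Neither stated sensitivity analysis would display this range.

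**The case against.** **LOCF may well be cautious here.** The article ties its dropout worry to web-based interventions (2.5.2, 3.1), which only the intervention arm uses. Section 2.3.1 describes a measure against waitlist dropout and does not forecast it. Waitlist participants get the program only after the last measurement, payment depends on completing all assessments, and both groups are reminded. All of this stands. It makes the shrinking direction at least as likely as the other, but it does not make the method conservative by construction.

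**The sizes depend on assumptions.** This also stands. The 30% versus 10% split is nowhere in the article, placing all dropout straight after baseline is the harsher case, and no passage suggests that an early gain fades completely.

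**A reader might infer that the trial's type I error is inflated.** The documents do not support that. The confirmatory test is the multilevel interaction, and the 8% to 10% belongs to a sensitivity analysis. In the scenarios simulated, dropout does not depend on outcome, so the mixed model remains unbiased and a divergence from LOCF would be visible.

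**A reader might also infer that no planned analysis departs from missing at random.** That goes too far, because LOCF does. What is lacking is a graded and plausible departure.

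**An unseen analysis plan or the supplementary R script may add more.** Possibly. But the article itself counts the sensitivity analyses as two and prints the label without qualification, so this is a stated choice and not a detail left out for brevity.

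**Conclusion.** The point holds in a limited form. The unqualified label is unsupported, because the sign of the LOCF bias depends on which arm loses more participants, when they leave, and how each arm changes. A false benefit from unequal dropout needs both waitlist improvement and more, or earlier, waitlist loss. Under the assumed scenarios the method moves the estimate by about a tenth of an SD towards the intervention, or by about two tenths against it. Separately, neither stated sensitivity analysis addresses in graded form the selective completion that section 2.5.2 itself raises.

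This should be corrected before the results are interpreted, but it does not threaten the trial. The confirmatory model and the sample size stand, and the documents do not show that LOCF will in fact favour the intervention.

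**What to change.** In section 2.5.2:
- Delete the word conservative.
- Replace LOCF with reference-based multiple imputation, in which intervention dropouts follow the waitlist trajectory. Alternatively, keep LOCF only as a secondary comparison, with its no-change assumption stated.
- Add an arm-specific delta-adjusted tipping-point analysis that reports how much worse the dropouts must be before the conclusion changes.
- Label the completer results as descriptive.

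The cost is a few lines of R and some wording, with no new data. If LOCF is dropped, comparison with older trials that used it becomes harder.

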#### Secondary confirmatory outcomes

2.4.5

•Changes in global eating psychopathology: Global eating psychopathology will be investigated as a secondary outcome using the total score of the EDE-Q (Hilbert et al., 2007), which is derived from the dimensions of *weight concern*, *shape concern*, *eating concern*, and *restraint*. The eating psychopathology dimensions are assessed with 22 items on a 7-point Likert scale and Cronbach's α ranges between .85 and .93 for the subscales and .97 for the total score (Hilbert et al., 2007).•Changes in the weekly frequency of binge eating episodes, overeating, and regular eating: The *Weekly Binges Questionnaire* (WBQ; Munsch et al., 2007; Munsch et al., 2019) will be used as a continuous method to monitor the frequency of objective and subjective binge eating episodes and overeating as secondary outcomes of BED symptom alterations. Weekly text messages throughout the study period will remind participants to report the occurrence and rate the severity of each of these eating episodes as well as regular eating within the last week on an 11-point scale (Munsch et al., 2007; Munsch et al., 2019).•Changes in eating-disorder-related clinical impairments: To assess hypothesized reductions in clinical impairments specific to eating disorders, we will employ the *Clinical Impairment Assessment* scale (CIA; Bohn et al., 2008), which measures overall and domain-specific impairments (i.e., cognitive, social, and personal). The CIA consists of 16 items rated on a 7-point Likert scale and demonstrates excellent internal consistency (Cronbach's α = .97), construct validity, and sensitivity to change (Bohn et al., 2008).•Changes in well-being: To measure assumed increases in well-being, we will use the frequently employed *World Health Organization-Five Well-Being Index* (WHO-5; Bech et al., 2003). The WHO-5 assesses general well-being based on five items, rated on a 6-point scale, and has high internal consistency (Cronbach's α = .92; Brähler et al., 2007).•Changes in work capacity: To address the increasing significance of health economic evaluations (Jenkins et al., 2021; Safi et al., 2022), changes in work capacity and productivity will be measured based on the *iMTA Productivity Cost Questionnaire* (iPCQ; Bouwmans et al., 2015). The iPCQ examines absences from work and productivity losses due to sickness-related restrictions in work efficiency. Test-retest reliability of the iPCQ is excellent concerning the reported number of sick leave days (ICC = .83) and moderate regarding the number of days at work while impeded (ICC = .56) and efficiency rates (ICC = .73; Bouwmans et al., 2013).

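### The multiple-imputation model names four predictors but not treatment arm, so this sensitivity analysis shrinks a true effect by about the missing fraction

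*Protocol article*

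**What the plan says.** Section 2.5.2 plans both completer and intent-to-treat analyses, and adds: "The treatment effects across the samples will be tested using two sensitivity analyses". One is last observation carried forward. The other is multiple imputation by chained equations, with predictors given as "BMI, global eating psychopathology, number of binge-eating episodes determined in the EDE interview, and years since illness onset as predictors". The sentence does not mention treatment arm or the EDE-Q binge count, which is the primary outcome (section 2.4.4).

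Section 2.5.1 defines the treatment effect. The final mixed model compares change between the groups "by adding the treatment × time interaction", with assessments at 0, 6 and 12 weeks.

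Section 2.3.1 fixes when the interview takes place: "After completing the diagnostic interview and the baseline assessment, randomization will be performed in a 1:1 ratio". The schedule in Table 2 also places the EDE interview at enrollment only. The same section says that, for blinded analysis, "an independent researcher will delete all information in the data set indicating the group membership". The article does not say how arm, even in masked form, reaches the imputation step.

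**The concern.** An imputation model has to contain the terms that the later analysis will test. Here the analysis tests arm by time, and the imputation model as named contains no arm. The interview binge count is measured before randomization, so it cannot stand in for arm. BMI and years since onset say nothing about allocation in a randomized trial. A missing follow-up value in either arm is therefore drawn from one common distribution, and the patients with imputed values dilute the arm difference seen in the others.

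This analysis is one of only two stated checks on dropout, and sections 2.5.2 and 3.1 both expect dropout to be notable. A built-in shrinkage could be read as evidence that a real result does not survive missing data.

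**Working it through.** **Inputs from the protocol article.** d = 0.50, intraclass correlation .40, power .80, alpha .05, N = 152, dropout of 20% considered in supplementary power analyses (all section 2.6); 1:1 allocation (2.3.1); visits at 0, 6 and 12 weeks (2.5.1). Assumptions: two-sided testing, normal outcomes, baseline complete, missingness completely at random, missing fractions other than 20%, and global eating psychopathology taken at baseline.

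**Step 1: reproduce the plan's sample size.** Take a random-intercept growth model with baseline SD 1 and residual variance 1 − 0.40 = 0.60. The squared deviations of the times 0, 6 and 12 from their mean sum to 72. The variance of the fitted 12-week change per patient is 144 × 0.60 / 72 = 1.20. Then n per arm = 2 × (1.960 + 0.842)² × 1.20 / 0.50² ≈ 75.4, rounded up to 76, so N = 152. Power at 76 per arm is .803. The stated figure is reproduced, without dropout, and it does not depend on the imputation model.

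**Step 2: analytic shrinkage, arm omitted.** Let f₁ and f₀ be the missing fractions at 12 weeks in the intervention and control arms, and δ the true difference. Patients observed at 12 weeks come from the intervention arm in proportion p = (1 − f₁) / (2 − f₁ − f₀). Imputed values in both arms are then centred at pδ on the scale where the control mean is zero. The expected difference is

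(1 − f₁)δ + f₁pδ − f₀pδ = δ[(1 − f₁) + (f₁ − f₀)p].

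- Equal fractions f: δ(1 − f). At 20%, 0.50 × 0.80 = 0.40.
- 30% intervention, 10% control: p = 0.70/1.60 = 0.4375; 0.50 × (0.70 + 0.20 × 0.4375) = 0.39.
- 40% intervention, 20% control: p = 0.60/1.40 = 0.429; 0.50 × (0.60 + 0.20 × 0.429) = 0.34.
- δ = 0: the result is 0 whatever the missing fractions.

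**Step 3: simulation.** There were 152 patients and a true d of 0.50. Half of those missing week 12 also missed week 6. Each run used ten proper normal-regression imputations and Rubin's rules, with 800 runs per scenario. Each cell gives the mean estimated d and, in brackets, the rejection rate.

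| Missing at 12 weeks | Four listed predictors | Plus baseline and 6-week outcome, no arm | Plus arm only | Plus arm and outcomes |
|---|---|---|---|---|
| 10% | 0.45 (.68) | 0.45 (.68) | 0.50 (.77) | 0.50 (.78) |
| 20% | 0.40 (.53) | 0.41 (.59) | 0.49 (.68) | 0.50 (.72) |
| 30% | 0.34 (.34) | 0.36 (.42) | 0.50 (.67) | 0.50 (.68) |
| 40% | 0.30 (.22) | 0.32 (.31) | 0.50 (.58) | 0.50 (.62) |

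The Monte Carlo standard error of the mean estimate is about 0.007. The first column follows (1 − f) × 0.50.

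**Step 4: separate the two omissions.** At 20% missing, adding outcomes without arm moves the estimate from 0.40 to 0.41; adding arm alone moves it to 0.49. Arm drives the bias. The outcome counts then raise power from .68 to .72.

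**Step 5: separate imputation from dropout.** Losing 20% of 152 leaves about 122 patients, or 61 per arm, and the formula in Step 1 then gives power .71. The .72 under the fuller imputation model is thus roughly the cost of dropout itself. The further fall to .53 comes from omitting arm.

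**The case against.** The strongest reply is that the list may name only auxiliary variables added to the analysis variables, with the full predictor matrix in the R script (Supplement S2), which is not shown. The sentence does not say that these are the only predictors. That limits certainty about what will be run. It does not rescue the text: the article itself states the predictors for a test of treatment × time, and nothing shown adds arm.

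A second reply is that global eating psychopathology has no stated time point and the EDE-Q total is also measured at 6 and 12 weeks. Follow-up scores would carry some indirect information on arm, but they would often be missing for the same patients. Even the primary outcome at 6 weeks, where observed, recovered very little of the bias in the table.

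Three stronger readings are tempting, and the documents do not support them.

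- A reader might infer that the shrinkage occurs whatever the truth. With no true effect there is none. If intervention dropouts benefited less than completers, a possibility that section 2.5.2 itself raises, imputation with arm could overstate the effect and these figures would not measure bias.
- A reader might infer that leaving out the 6-week count and the weekly reports also causes the bias. Step 4 shows that the 6-week count makes little difference to it. The weekly reports were not simulated, and they may stop when a patient drops out.
- A reader might infer that the confirmatory result is compromised. Imputation is one of two sensitivity analyses, and the mixed model in section 2.5.1 is separate from it. The error runs towards zero, so it does not favour a false claim of benefit.

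**Conclusion.** The point holds for the imputation analysis as written. Omitting arm makes the imputation model incompatible with the effect it is meant to check. Given a true effect and data missing at random within arm, the estimate falls by about the missing fraction: from 0.50 to about 0.40 at 20% missing, with power about .53 instead of .72. The power figures rest on normal outcomes missing completely at random. Only the 20% comes from the document; from 10% to 40% missing the estimate runs from 0.45 down to 0.30. The primary mixed model stands. This is a should-fix: a robustness check that could wrongly make a real effect look fragile.

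**What to change.** In section 2.5.2, add treatment arm to the imputation model, together with the EDE-Q binge counts at baseline, 6 and 12 weeks, so that it matches the analysis model. Keep the four listed variables as auxiliaries and state the time point of global eating psychopathology. Arm removes the bias; the outcome counts serve precision and make missing at random more plausible. Because section 2.3.1 removes group information from the data set, state that the independent researcher supplies a masked arm code. The treatment × time model needs one in any case.

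Weekly Binges Questionnaire counts, separate imputation by arm and predictive mean matching are optional. If Supplement S2 already includes arm, only the text needs correcting.

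The cost is a sentence or two in the plan and, if needed, a changed predictor matrix in the script. No new data are required. The change should be fixed before the data are analysed.
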